### Statistical analysis

Regarding the primary endpoint, the clinical cure rate with 95% confidence intervals will be compared between the short-course therapy group (24–72 h) and the standard-course therapy group (96–168 h) in the full analysis set (FAS), which will include all registered participants who receive any part of the treatment protocol. Subgroup analyses will be conducted based on severity, age, AC etiology, and other baseline factors using the confidence intervals of the differences and logistic regression models. Interaction effects will be examined. The primary analysis population is the FAS; however, analyses using the per-protocol set (PPS), which includes participants from the FAS who had no study protocol violations and were compliant with the protocol, will also be conducted to confirm that the same conclusions are drawn from both sets.

Secondary endpoints will also be examined in both the FAS and PPS sets; these will include the following variables within 30 days: the recurrence and mortality rates, required days of antibiotic use, required days of hospitalization, and treatment costs.

A safety analysis will be conducted among the participants who received the study treatment at least once. All adverse events will be reported, and serious adverse events (SAE) will be tallied separately. Adverse events observed after administration of the trial drug will be tabulated by group, and the number of occurrences, cases, and incidence rates will be calculated and compared between groups. All adverse events will be analyzed, regardless of causality. Descriptive statistics will be calculated by group for clinical laboratory tests, and clinically significant differences will be highlighted. Other parameters will be analyzed by variable type; descriptive statistics will be calculated for continuous variables and frequencies tallied for categorical variables in each group.

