Continuous variables will be reported as medians with interquartile ranges, and categorical variables will be reported as numbers with percentages. Continuous and categorical variables will be compared using the Mann–Whitney *U* and chi-square tests, respectively. Risk differences with 95% confidence intervals (CIs) will be calculated for binary outcomes, and the two-sided significance level for all tests will be set at *p* < 0.05. All statistical analyses will be performed using EZR (Saitama Medical Center, Jichi Medical University, Saitama, Japan), a graphical user interface for R version 4.2.3 (R Foundation for Statistical Computing, Vienna, Austria), which is a modified version of the R commander designed to include additional biostatistical functions (48).

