## Discussion

This trial assesses whether short-course antibiotic therapy of 24–72 h for AC with appropriate biliary drainage is non-inferior to standard-course therapy of 96–168 h. A retrospective cohort study indicated comparable effectiveness between short-course and standard-course therapy for AC, with complications appearing to be more frequent with standard-course therapy (14–16,49). Should short-course therapy prove to be non-inferior, it may offer several advantages over standard-course therapy, including shorter hospital stays, reduced potential side effects from antibiotic treatment, lower costs, and a decreased likelihood of developing antibiotic resistance (1–6). However, if the non-inferiority of the trial treatment is not demonstrated, then the current standard treatment duration will be considered necessary and sufficient for this population.

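### Antibiotic days, hospital days and treatment costs are compared only by medians and a rank test, so the saving gets no interval and the median can misstate average use

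*Protocol article*

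**What the plan says.** All of this is in the protocol article.

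- **Endpoints.** The Statistical analysis section names, among the secondary endpoints over 30 days, "required days of antibiotic use, required days of hospitalization, and treatment costs". Outcome measures words the antibiotic and hospital endpoints as total numbers of days.
- **Summary.** The Statistical analysis section gives one rule: "Continuous variables will be reported as medians with interquartile ranges, and categorical variables will be reported as numbers with percentages".
- **Comparison.** "Continuous and categorical variables will be compared using the Mann–Whitney" U test and the chi-square test respectively, and "the two-sided significance level for all tests will be set at" 0.05.
- **Estimates with intervals.** "Risk differences with 95% confidence intervals (CIs) will be calculated for binary outcomes". No counterpart is given for continuous outcomes. For other parameters the section promises only that "descriptive statistics will be calculated for continuous variables and frequencies tallied for categorical variables in each group".
- **Intended reading.** If non-inferiority is shown, the Discussion foresees several advantages, "including shorter hospital stays, reduced potential side effects from antibiotic treatment, lower costs" and less resistance.

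**The concern.** Days and costs add up across patients. A hospital or payer that wants to know what a shorter course saves needs the arithmetic mean, because mean times number of patients gives the total. The median describes the typical patient and hardly moves when a few patients have very long courses or stays.

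The protocol article provides for such patients. Its section on extending antibiotics allows up to 14 days in some cases and longer in others, and recurrence by definition means restarting antibiotics. If a shorter course does harm, this is where it would show.

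Two things are at stake. First, the trial accepts a cure rate up to 10 points lower partly in return for fewer days and lower cost, yet plans no interval for that return. A rank-test p-value gives neither its size nor its precision. Second, if failures are more frequent in the short arm, the difference in medians overstates the average saving.

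**Working it through.** **1. The plan's own figure.** With 95% cure in both arms, margin 0.10, one-sided 2.5% and 90% power:

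n per arm = (1.960 + 1.282)² × 2 × 0.95 × 0.05 / 0.10² = 10.51 × 0.095 / 0.01 = 99.8, so 100.

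This reproduces the stated 100 per arm. It is not in dispute. It supplies the planned failure rate (5%) and the margin.

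**2. Inputs for the illustration.** The documents give no mean, SD or cost figure for these endpoints, so the following are assumptions:
- index stay is gamma with shape 9 and mean 8 days (SD 8/3 = 2.67);
- each failure adds 14 days;
- failure is 5% in the standard arm and f in the short arm;
- the short course saves s days for every patient;
- 105 patients per arm, as in the protocol article, and stays rounded to whole days.

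**3. Hospital days.** The mean difference (short minus standard) is exact: −s + 14 × (f − 0.05). The median difference is the average over several thousand simulated trials.

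| s (days) | f | Median difference | Mean difference |
|---|---|---|---|
| 1 | 5% | −1.0 | −1 + 0 = −1.0 |
| 2 | 10% | −1.8 | −2 + 0.70 = −1.3 |
| 0.5 | 10% | −0.3 | −0.5 + 0.70 = +0.2 |
| 1 | 14% | −0.7 | −1 + 1.26 = +0.26 |

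With equal failure the measures agree. With 10% failure and a 2-day saving, the median overstates the average saving by about half a day.

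**4. When the sign would reverse.** The mean difference is zero when f − 0.05 = s/14. That is 3.6 points for s = 0.5, 7.1 points for s = 1 and 14.3 points for s = 2. The last lies beyond the 10-point margin.

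**5. The interval that is not planned.** The variance of stay is 2.67² + 14² × f(1 − f).
- Standard arm: 7.11 + 196 × 0.0475 = 16.42.
- Short arm at 10% failure: 7.11 + 196 × 0.09 = 24.75.
- Standard error of the mean difference: √[(16.42 + 24.75)/105] = 0.63. The half-width is 1.96 × 0.63 = 1.23 days.

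For s = 2 and f = 10% the interval is about −2.5 to −0.1 days. A reader given two medians and a p-value would not see how loosely the average saving is known.

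**6. Antibiotic days.** Assume 3 days in the short arm and 5 in the standard arm, with 5 of 105 standard patients on 14 days. The standard mean is (100 × 5 + 5 × 14)/105 = 5.43. With 10 of 105 short-course patients on 14 days, the short mean is (95 × 3 + 10 × 14)/105 = 4.05. The median saving is 2 days and the mean saving 1.38. A reversal needs a share (5.43 − 3)/(L − 3) of the short arm on a course of L days: 22% for 14 days, 13% for 21 days, 9% for 30 days.

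**7. The primary test.** The interval method is not specified in the article, so a Wald interval is assumed. With 5 of 105 standard-arm failures:
- 8 short-arm failures give an upper limit of 0.029 + 1.96 × 0.0332 = 0.094, which passes;
- 9 give 0.038 + 1.96 × 0.0343 = 0.105, which fails.

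**The case against.** A reader might infer that the trial could announce a saving while average use is in fact higher. The documents do not support this as a likely outcome. The Discussion makes the benefits conditional on non-inferiority, and a reversal needs an excess of failures that the primary test would usually catch. In the two reversing rows of the table (10% and 14% failure), a significant rank-test saving together with a higher mean occurred in about 0.1% and 1.4% of simulated trials. It never occurred together with demonstrated non-inferiority in 3,000 runs of each.

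Heavier assumed tails do reverse more often. With index stays of about 6 against 8 days and some 30-day stays (5% of the standard arm), both features appeared in 41% of trials at a 12% short-arm tail. But if those patients are cure failures, about 13 against 5 of 105 would fail the primary test. That answer is incomplete, since a long stay need not be a cure failure. It still leaves the reversal a remote possibility.

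A reader might also infer that the plan gives no effect size. That goes too far: the arm medians can be subtracted. What is absent is a between-arm estimate with an interval. Nor does the case for a shorter course rest on days and cost alone, since resistance and adverse events are also given as reasons.

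Medians with a rank test are conventional for skewed data, these endpoints are secondary, and an unseen analysis plan may add estimators. This lowers the weight of the point but does not remove it. The article states a rule for every continuous variable and names intervals for binary outcomes only, so the choice is stated and not merely left open.

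**Conclusion.** The point stands as a minor improvement. As written, antibiotic days, hospital days and treatment costs get no mean and no between-arm difference with an interval, so neither the size nor the precision of the average saving would be reported. The interval is missing whatever the failure rates turn out to be.

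The median's misstatement of average use depends on assumption. It is about half a day of stay (1.8 against 1.3) for a 2-day saving with 10% against 5% failure and 14 extra days per failure, and nil when failure is 5% in both arms as planned. No comparable figure can be given for costs, because the documents contain no cost data. A change of sign needs a small saving together with a clear excess of failures, and is unlikely in a trial that shows non-inferiority. The sample size and the primary conclusion are unaffected.

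**What to change.** In the Statistical analysis section, add for these three endpoints within 30 days: the arithmetic mean per arm, and the difference in means with a bootstrap or robust 95% confidence interval. Apply this in both analysis sets in which the secondary endpoints are examined. Keep the medians, interquartile ranges and Mann–Whitney test alongside. Settle the wording before the data are analysed.

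The cost is a few lines of text and minor extra analysis. No new data and no change in sample size are needed. With skewed data the interval for the mean difference will be fairly wide, and in the reversing examples it would include zero in about 93% of trials. It therefore shows how uncertain the average saving is and will not by itself prove a reversal.

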### Sample size

The clinical cure rates for short- and standard-course therapies were estimated using our retrospective dataset. According to a dataset of 361 patients that closely matched the control group in this trial, the clinical cure rate was 95.1% (135/142) in the short-course therapy group and 95.0% (208/219) in the standard-course therapy group, with an overall rate of 95.0% (343/361). This is consistent with the results reported in the literature (46,47). Therefore, a clinical cure rate of 95% was used in both groups for sample size calculation in this trial. The number of patients required for analysis was determined to be 200, with 100 cases per group, assuming a one-sided significance level of 2.5%, power of 90%, and a non-inferiority margin of 10% (39). Anticipating loss to follow-up and other contingencies, the target enrollment was set at 210, with 105 cases per group.

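### Cure split by fever at the end of antibiotics is a post-randomisation subgroup, read on days 1–3 in one arm and 4–7 in the other, so its between-arm comparison can favour the short course with no true effect

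*Protocol article*

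**What the plan says.** The Outcome measures section of the protocol article lists nine secondary outcomes of the form cure rate by some characteristic. One of them splits patients by whether fever is present or absent when antibiotic treatment ends. The other eight are severity, age 75 or over, blood culture, bile culture, susceptibility before ERCP, antibiotic duration before ERCP, time from admission to ERCP, and etiology. These describe the patient or the episode up to about the time of ERCP (I assume that bile is sampled at ERCP).

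Randomisation takes place within 24 h of successful drainage. Treatment then lasts 1–3 days after drainage in the short arm and 4–7 days in the standard arm (Trial interventions).

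The Statistical analysis section says that subgroup analyses rest on severity, age, etiology and further baseline characteristics, using confidence intervals of differences and logistic regression. It adds that "Interaction effects will be examined" and that "the two-sided significance level for all tests will be set at *p* < 0.05".

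**The concern.** A subgroup comparison between arms is fair when membership could have been read before allocation, because randomisation then balances the arms inside each stratum. Fever at the end of treatment is read later, and the assigned arm decides how much later. A patient febrile on day 2 may simply be recovering at an ordinary pace. A patient still febrile on day 5 is a slow responder. The febrile stratum therefore holds a broad mix in the short arm and a small, sicker remnant in the standard arm. The afebrile strata differ in the opposite way: the short arm's has lost its slower responders, while the standard arm's has kept most of them.

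The outcome adds to the problem. Cure requires, among other things, that fever resolves within 14 days of ERCP. Someone febrile at a stop on day 1–3 has 14 − 3 = 11 to 14 − 1 = 13 days left to meet that condition. Someone febrile at a stop on day 4–7 has 14 − 7 = 7 to 14 − 4 = 10.

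What is at stake is how the trial will be read on a practical question: whether antibiotics can be stopped while the patient is still febrile. The planned split looks as if it answers this, but a between-arm reading of it is biased, and a larger sample would not remove the bias.

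**Working it through.** The plan gives no figure for this split, so there is nothing to reproduce. The check is whether a between-arm difference can arise when duration does nothing.

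**Inputs from the article.** Cure is 95% in each arm: "a clinical cure rate of 95% was used in both groups for sample size calculation in this trial". Enrolment is 105 per arm. Antibiotics stop on day 1–3 v day 4–7.

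**Assumptions (not in the article).** Fever duration T is lognormal with median 1 day and log-scale standard deviation s = 0.8. The stop day U is uniform over the arm's window and independent of T. A latent severity links longer fever to failure, from weakly to strongly. Duration of treatment has no effect on cure.

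**Step 1: share febrile at stop.** For each arm this is the average over U of 1 − Φ(ln U / s).

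- Short arm, U on 1–3: 22.5%. Standard arm, U on 4–7: 1.9%.
- With s from 0.7 to 1.0 the shares run from 20% to 27% and from 1% to 5%.

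**Step 2: expected stratum sizes.** Short arm: 0.22 × 105 ≈ 23 patients. Standard arm: 0.02 × 105 ≈ 2 patients. The chance that the standard arm has no febrile patient at all is 0.98^105 ≈ 12%.

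**Step 3: cure by stratum with no duration effect** (2,000,000 simulated patients).

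| Link between fever and failure | Febrile: short v standard | Afebrile: short v standard |
|---|---|---|
| Weak | 93% v 92% | 95.3% v 95.0% |
| Strong | 90% v 79% | 96.6% v 95.3% |

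**Step 4: consistency check.** Weighting the strata should return 95% in each arm.

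- Strong link, short: 0.22 × 0.90 + 0.78 × 0.966 = 0.198 + 0.753 = 0.951.
- Strong link, standard: 0.02 × 0.79 + 0.98 × 0.953 = 0.016 + 0.934 = 0.950.
- Weak link, short: 0.22 × 0.93 + 0.78 × 0.953 = 0.205 + 0.743 = 0.948.
- Weak link, standard: 0.02 × 0.92 + 0.98 × 0.950 = 0.018 + 0.931 = 0.949.

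Apart from rounding, the arms have the same overall cure. The short arm still looks better in both strata, because the two arms are divided at different points of the same recovery curve.

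**Sensitivity.** A separate run with other assumptions gave 94% v 92–93% among the febrile for a weak link and 86–88% v 64–76% for a strong one. The direction was the same throughout; the size was not.

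**The case against.** **The split may be prognostic only.** The outcome list does not say that the arms will be compared within fever strata. Restricting subgroups to baseline characteristics could be taken to exclude it, and the Discussion's remark that persistent fever does not affect outcomes suits a prognostic reading. That reading is possible but not stated. The item stands among eight ordinary subgroup splits in a trial that compares two arms, so one sentence is needed to settle it.

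**The illustration rests on assumptions.** This stands for the size. Fever may also move the stop day. The section on extending antibiotics allows a change or extension for temperature above 37.5 °C on the third day of enrollment, whereas the Discussion says duration is not altered for persistent fever, with listed exceptions. Those two passages need to be reconciled. If fever can move the stop day, the stratum is still defined after randomisation.

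**Two patients cannot support a claim.** This also stands. A febrile contrast based on about 2 standard-arm patients would be very imprecise, and the afebrile distortion is only 0.3 to 1.3 points. That limits the damage, but it also shows that the comparison has little to offer.

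**A stronger reading: multiplicity.** A reader might infer that a 0.05 level for all tests, over a long unranked list of secondary outcomes, makes a chance benefit of the short course likely. The documents do not support this. A per-test 0.05 level is conventional, no family-wise rate is stated, and a hierarchy or exploratory label is commonly left to a full protocol or analysis plan, which is not shown. Nor is "likely" borne out. For 9 independent comparisons with no true difference, the chance of at least one nominal result in either direction is 1 − 0.95^9 = 37%, and of one favouring the short course 1 − 0.975^9 = 20%. Correlation lowers the first to 27% (at 0.5) or 17% (at 0.8). The Discussion says only that the short course may offer advantages such as shorter stay and lower cost; no superiority claim on them is planned.

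**Conclusion.** The point holds for the fever split alone. As listed, it is a subgroup formed after randomisation, at a time set by the assigned arm, and it does not fit the article's own description of subgroups as baseline ones. A between-arm comparison within its strata can favour the short course when duration has no effect.

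The illustrative size is 1 to 11 points among the febrile and 0.3 to 1.3 points among the afebrile, given a 1-day median fever duration, a stop day independent of fever, and a weak to strong link between fever and failure. The direction needs only that slower defervescence goes with a lower chance of cure.

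A reader should not infer that the main result is at risk. The primary comparison in the full analysis set, its one-sided 2.5% error rate and the sample size of 200 analysable patients do not depend on this split.

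**What to change.** In the Outcome measures section, or in the analysis plan before database lock:

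- Take fever at the end of antibiotic treatment out of the between-arm subgroup comparisons.
- Use fever at registration, or another fever measure taken before randomisation, for the subgroup analysis.
- State that end-of-treatment fever will be reported descriptively within each arm, as the number febrile at stop and the number of those cured, with no test or interaction between arms.

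The cost is a few sentences, with no extra patients and no change to the sample size; a pre-randomisation temperature should already be available from the diagnostic work-up. The small downside is that the trial no longer offers a between-arm contrast for patients who stop while febrile. A sentence calling the secondary and subgroup results exploratory would be a harmless addition, but is optional.

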### Trial oversight

This study will be conducted at the Center for Gastroenterology of the Shonan Kamakura General Hospital. The data center is co-located with data management personnel to facilitate overseeing centralized data monitoring throughout the trial period. The Operations Committee played a role in formulating the protocol and will supervise the progression of the trial (Table 2). No patients or members of the public were involved in the design of this study.

**Table 2 Tab2:** Steering Committee

Role in this study	Name	Institution
Principal Investigator	[name]	Department of Gastroenterology Medicine Center, Shonan Kamakura General Hospital
Supervision/Overall Guidance	[name]	Division of Medical Oncology/Hematology, Department of Medicine, Kobe University Graduate School of Medicine
Research Support	[name]	Clinical Research Support Office, Shonan Kamakura General Hospital
Research Collaborator	[name]	Clinical Trial Center, Shonan Kamakura General Hospital
Data Management	[name]	Department of Gastroenterology Medicine Center, Shonan Kamakura General Hospital
Event Adjudication Committee	[name]	Department of Gastroenterology and Hepatology, Tokyo Medical University
Event Adjudication Committee	[name]	Genomic Medicine Research Project, National Center for Global Health and Medicine
Event Adjudication Committee	[name]	Department of Gastroenterology and Hepatology, Kitasato University School of Medicine
Study Statistician	[name]	Department of the Institute of Biomedical Research, Sapporo Higashi Tokushukai Hospital
Study Secretariat		Shonan Kamakura General Hospital
Project Management		Shonan Kamakura General Hospital

The principal investigator reviews cumulative enrollment each month and sends a progress report via email to all collaborating sites, encouraging additional recruitment as needed. An investigator kick-off meeting was held at study launch, and the principal investigator remains in close contact with participating sites by email or teleconference so that even minor operational issues can be resolved promptly.

Because all antibiotic therapy is delivered by intravenous infusion under the direct supervision of healthcare professionals, patient-side adherence measures (e.g., tablet counts) are not applicable. At the initiation meeting, all sites were instructed to follow the protocol strictly.

At the coordinating center, both a Clinical Research Center and a Clinical Trial Center have been established. Clinical Research Centers are also present at each participating site. The Clinical Research Centers are responsible for protocol development and amendments, and coordination with participating sites. The Clinical Trial Center provides operational advice and liaises with monitoring and auditing bodies. Several full meetings were held at the start of the study. Although regular full meetings are not planned to be held after that point, close consultations are conducted with the principal investigator whenever needed to support decision-making and trial management—even on minor matters.

In case of any protocol amendments, the principal investigator will notify all participating centers of the changes. A copy of the revised protocol will be filed in the Investigator Site File at each site. Any protocol deviations will be documented using a breach report form. The clinical trial registry entry (e.g., jRCT) will be updated accordingly.

